### **8.3 Multivariate analysis**

Multiple linear regression analyses will be performed to determine the independent contribution of gender, age and BMI on energy expenditure, substrate oxidation, (muscle) protein synthesis and sleep. All statistical tests will be two-sided and differences will be considered statistical significant if  $p < .05$ .

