### 3. STUDY DESIGN

[figure not shown]

**Figure 1:** Flow diagram of study design.

The study will have a parallel design and will consist of a short-term (1 week) and long-term (12 weeks) dietary intervention period.

Two days before the baseline measurement, subjects will be fed in energy balance (EB) with protein intake of 15En%. After the baseline measurement, subjects (n=40) will be randomly divided in two groups (2 x n=20). The two applied conditions will differ in the absolute protein content of the meals, including 5En% and 30En% from protein. Fat content will be kept constant in all three conditions regarding the possible effects of fat intake on fat oxidation, resulting in macronutrient compositions of the diets of En% Protein/Carbohydrate/Fat: 5/60/35 and 30/35/35. Both conditions will be compared with the baseline measurement when subjects are fed in energy balance with a macronutrient composition of 15/50/35 En% (Protein/ Carbohydrate/Fat). During the 12 weeks dietary intervention period, subjects will receive recipes prescribed by a qualified dietician. The 30En% protein group will receive recipes for high-protein meals and in addition protein supplements. The 5En% protein group will receive recipes for low-proteins meals and in addition carbohydrate supplements.

To determine energy expenditure and substrate oxidation, subjects will stay in the respiration chamber for 48 hours at baseline, after 1 week and after 12 weeks of an energy balanced diet. During the stay in the chamber, polysomnography will be used to measure wake and sleep phases continuously, in order to determine sleep duration and sleep quality. Every morning blood samples will be taken in fasted state to determine plasma concentrations of glucose, insulin and free fatty acids. Appetite and mood profiles will be measured hourly and before and after each meal, by anchored 100mm visual analogue scales and by POMS and STAI-state questionnaires.

At the start and after 12 weeks, 3-compartment body composition will be determined with the deuterium dilution technique combined with densitometry (BodPod). To investigate fat distribution MRI and  $^1\text{H}$ -MRS will be used. Abdominal fat will be assessed at baseline, and liver fat and intramyocellular lipid (IMCL) content, as well as the mass of the vastus lateralis muscle will be measured at baseline and after 12 weeks.

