#### 4.4 Sample size calculation

To do a sample size calculation a respiration chamber study on the effect of two diets with different macronutrient compositions on energy expenditure was used.

Westerterp *et al.* 1999 report Diet-induced-Thermogenesis of  $14.6 \pm 2.9$  % and  $10.5 \pm 3.8$  % when changing from 29% of energy from protein to 9% of energy from protein in the diet (12). Sample size was calculated using G\*Power version 3.2.1. With the group mean Diet-induced-Thermogenesis change from the past research (12), G\*Power first calculates the effect size. The calculated effect size was 1.212986. With an  $\alpha$  of 0.05 and  $\beta$  of 0.10 (power= $1-\beta=0.90$ ) and an effect size of 1.212986, the program calculates that we need 16 subjects per group.

Taking into account a drop out rate of  $\pm 20\%$ , 20 subjects per condition will be included.

When the subject leaves the respiration chamber before the end of the measurement, this subject is considered as a drop-out.

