## 6. METHODS

### 6.1 Study parameters/endpoints

#### 6.1.1 *Main study parameter/endpoint*

The main study parameters are energy expenditure, substrate oxidation and sleep.

- energy expenditure (MJ/day), which will be measured via oxygen consumption and carbon dioxide production in the respiration chamber
- substrate oxidation (gram/day); carbohydrate, fat and protein oxidation will be calculated using oxygen consumption, carbon dioxide production and urinary nitrogen excretion, with the formule of Brouwer (39). Urine will be collected during the stay in the respiration chamber. Nitrogen concentration will be measured using a nitrogen analyser.
- sleep (minutes) will be registered continuously with polysomnography

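### No specified analysis gives a diet effect on energy expenditure or substrate oxidation adjusted for baseline or body size, although baseline chamber values and fat-free mass are collected

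*Protocol*

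**What the plan says.** **Endpoints.** Section 6.1.1 defines the first main parameter as "energy expenditure (MJ/day), which will be measured via oxygen consumption and carbon dioxide production in the respiration chamber". Substrate oxidation is in grams per day and sleep in minutes. Neither energy expenditure nor oxidation is scaled to body size.

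**Diet comparison.** Section 8.2 tests differences between the two conditions by one-way ANOVA with Bonferroni correction and names no covariates. The baseline measurement appears there only in parentheses, as something to compare with, not as a covariate. A later sentence in 8.2 announces multiple regression for between-subject effects without listing regressors.

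**Named regression.** Section 8.3 states: "Multiple linear regression analyses will be performed to determine the independent contribution of gender, age and BMI on energy expenditure, substrate oxidation", and goes on to muscle protein synthesis and sleep. Diet condition is not among the regressors.

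**Data at hand.** Section 3 places chamber stays at baseline, week 1 and week 12. For body composition it says: "At the start and after 12 weeks, 3-compartment body composition will be determined with the deuterium dilution technique". Section 6.1.2 lists fat-free mass in kg.

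**Size of the trial.** Section 4.4 says "The calculated effect size was 1.212986" and "the program calculates that we need 16 subjects per group". After an allowance for drop-out, "20 subjects per condition will be included".

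**The concern.** The primary objective is the response to diet. Sections 8.2 and 8.3 between them give either a diet comparison without covariates or a covariate model without diet. Neither gives an adjusted diet difference.

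For endpoints in MJ/day and g/day this matters more than usual. The trial enrols men and women, and these quantities depend on how large a person is; section 6.3.2 itself sets chamber intake at 1.4 times each subject's sleeping metabolic rate. In a covariate-free comparison, all of that variation between subjects stays in the error term.

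BMI would remove only part of it, because BMI divides height out. Fat-free mass in kg measures size directly. The subject's own baseline chamber value carries size and other stable differences as well. With 16 to 20 subjects per arm, precision is worth recovering when the data are already there.

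**Working it through.** **1. The protocol's own figure.** Inputs from 4.4: thermogenesis 14.6 ± 2.9% and 10.5 ± 3.8%, α 0.05, power 0.90; two-sided testing is stated in 8.3.

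- Pooled SD = √((2.9² + 3.8²)/2) = √11.425 = 3.380.
- d = (14.6 − 10.5)/3.380 = 1.213, as stated.
- Two-sample t-test (noncentral t): power is 0.894 at 15 per group and 0.913 at 16, so 16 per group reproduces.
- 16/(1 − 0.20) = 20, which also reproduces.

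The figure is arithmetically sound. It concerns thermogenesis in percent, so it does not show what 16 per arm delivers for MJ/day in a mixed-sex sample.

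**2. Why BMI is a weak size measure.** Weight = BMI × height². At BMI 23, a height of 1.60 m gives 23 × 2.56 = 58.9 kg and 1.90 m gives 23 × 3.61 = 83.0 kg. That is 24.1 kg apart at the same BMI. Gender would absorb part of this gap, but not the variation within each sex.

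**3. Effect of adjustment on the diet contrast.** Let R² be the share of the unadjusted residual variance that the added covariates explain. The standard error is then multiplied by √(1 − R²). The documents give no value for R², so the range is assumed. Power is for 16 per arm and a true difference of 0.8 unadjusted residual SDs (also an assumption), with four degrees of freedom spent on baseline value, gender, age and fat-free mass.

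| Assumed R² | SE multiplier | Power at 0.8 SD |
|---|---|---|
| unadjusted | 1 | 0.591 |
| 0 | 1.000 | 0.587 |
| 0.1 | 0.949 | 0.632 |
| 0.2 | 0.894 | 0.683 |
| 0.3 | 0.837 | 0.740 |
| 0.5 | 0.707 | 0.869 |

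For R² of 0.1 to 0.5, the standard error falls by 5% to 29%. The lost degrees of freedom cost 0.591 − 0.587 = 0.004 of power at 0.8 SD, and 0.913 − 0.910 = 0.003 at the planned 1.213.

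**4. Limit of step 3.** The table takes the covariates as balanced between arms. Under simple randomisation with q normally distributed covariates, chance imbalance multiplies the variance on average by 1 + q/(2n − q − 3). With q = 4 and n = 16 this is 1 + 4/25 = 1.16. The SE multiplier becomes √(0.9 × 1.16) = 1.02 at R² = 0.1 and √(0.5 × 1.16) = 0.76 at R² = 0.5. Section 4.1 intends groups matched on BMI, age and gender, which should limit this. Still, the gain is worth having only if the covariates are clearly prognostic, as the baseline value of the same chamber measurement can be expected to be.

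**The case against.** The case on the other side has several sound parts.

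- **8.3 is a predictor analysis.** It sets out to describe what gender, age and BMI contribute, and the diet test sits in 8.2. A predictor model without diet is not wrong in itself. This stands, and it is why the point is the missing adjusted diet analysis rather than a faulty 8.3.
- **The regression sentence in 8.2 is open.** It could cover a model containing diet arm, so a reader should not infer that the protocol rules out every adjusted diet analysis. It is too vague, however, to count as a specified one.
- **BMI has a stated basis.** Section 4.1 matches the groups on BMI, age and gender, the same three variables as in 8.3. Keeping BMI is defensible; the gap is the absence of diet, baseline value and a direct size measure.
- **Fat-free mass may add little** once the baseline chamber value is in the model. This also stands.

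Two stronger readings are tempting. A reader might take d = 1.213 from 4.4 and infer that leaving diet out of 8.3 inflates residual variance by 1.213²/4 = 37%, or standard errors by 17%. That would affect only the coefficients for gender, age and BMI, not the diet contrast, and it borrows an effect size on the percent-thermogenesis scale. It should not be used. A reader might also infer that body size is the main source of noise in all the endpoints. The documents do not quantify this for energy expenditure, and they give no ground for it for sleep or muscle protein synthesis.

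**Conclusion.** The point holds for energy expenditure and substrate oxidation. The protocol specifies a diet comparison without covariates and a covariate model without diet, so a diet effect adjusted for baseline or body size is nowhere specified, although the data for it are collected. This is not a source of bias: with random allocation the unadjusted comparison remains valid. What is lost is precision, and protection against chance differences between small arms.

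The size of the loss cannot be read from the documents. A 5% to 29% reduction in the standard error rests on an assumed 10% to 50% of residual variance explained and on balanced covariates. With simple randomisation the lower end would bring no gain on average, and the upper end about 24%. Most of any gain may come from the baseline value, with fat-free mass adding less.

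**What to change.** State the adjusted diet analysis in section 8, by endpoint:

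- **Energy expenditure and substrate oxidation:** ANCOVA of the week-1 and week-12 values on diet arm, baseline value of the endpoint, gender, age and baseline fat-free mass in kg. BMI may stay as a matching factor, for one more degree of freedom. Report the adjusted diet difference with its 95% CI.
- **Sleep:** diet arm and the baseline value; fat-free mass is not required.
- **Muscle protein synthesis:** add diet arm to gender, age and BMI. It is measured once, on an optional day after the last chamber stay, so there is no baseline value to adjust for.

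Use fat-free mass from the start of the trial, not week 12. Section 1 hypothesises that diet affects fat-free mass, so adjusting for the later value could remove part of the effect under study.

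The cost is a change of wording. No visit, measurement or subject is added.

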## **9. ETHICAL CONSIDERATIONS**

### **9.1 Regulation statement**

The study will be conducted according to the principles of the Declaration of Helsinki (9th version, October 2008, Seoul) and in accordance with the Dutch version of the Medical Research Involving Human Subjects Act (in Dutch: Wet Medisch-wetenschappelijk Onderzoek met mensen; WMO). Before the study will start, the Medical Ethics Committee of Maastricht University will approve the protocol and all relevant documents.

### **9.2 Recruitment and consent**

Subjects will be recruited by advertisements in local newspapers and on notice boards at the Maastricht University. They will be informed about the study by reading the provided written 'Subject information'. The researchers will orally check their comprehensiveness. An independent person who is well informed about the study could eventually provide additional information, and subjects will be referred to the CCMO brochure 'General information for research participants' that contains general information about medical-scientific research. After being well-informed subjects will get one week before they have to decide to participate in the study. All subjects will confirm their approval for participation by signing an informed consent form at the start of the screening.

### **9.3 Benefits and risks assessment, group relatedness**

Anthropometric measurements, performed during the screening, will not be invasive for the subjects. Blood sampling via venapuncture is limited to one sample during the screening and one sample per day in the respiration chamber. There are no side effects, except from a minor risk of bruising. Insertion of the catheters in a vein is comparable to venapuncture and here as well the only risk is a small local hematoma. This is the same for the muscle biopsy. The incision made for obtaining the muscle biopsy will be done by an experienced physician and will heal completely. The research group of [name]. [name] has extensive experience with taking muscle biopsies. During the follow up several days after taking the biopsy no complications have been reported.

The test beverages contain tested normal nutritional ingredients and for this reason do not form any health risks. The labeled amino acids tracers applied in this experiment are not radioactive and are completely safe. The production of the tracers for intravenous administration will occur in a sterile environment according to GMP guidelines.

Deuterium is an isotope of water that naturally appears in the body. Drinking it does not expose the subject to any risks. Urine sampling will be done in urine bottles added with diluted HCl, which might pose a risk for the subjects. However, subjects will be carefully

instructed on how to handle the bottles to reduce these risks. MRI and MRS are safe, non-invasive procedures with no ionizing radiation and these procedures do not expose the subjects to any risks if the exclusion criteria (no electronic implants, no pacemakers, no metal fragments in the eyes, skin or body) are well respected. Additionally, there are no risks for the subject in consuming any of the provided meals, because people with certain food allergies are excluded for participation and all food items will be commercially available in normal Dutch supermarkets. Studies in the respiratory chamber will be conducted using standard operating procedures. A pair of subjects will always participate in the study at the same time and therefore they will never be alone. The subjects will be able to contact the investigators during the entire night. In addition, they will be able to get out of the chamber at any time they feel uncomfortable. A 30En% protein or a 5En% protein diet for 12 weeks will not have any side effects on the subject's health.

This study does not have any benefits for the subjects themselves, but will give possible new knowledge for treatment of obesity.

#### **9.4 Compensation for injury**

The sponsor/investigator has a liability insurance which is in accordance with article 7, subsection 6 of the WMO.

The sponsor (also) has an insurance which is in accordance with the legal requirements in the Netherlands (Article 7 WMO and the Measure regarding Compulsory Insurance for Clinical Research in Humans of 23th June 2003). This insurance provides cover for damage to research subjects through injury or death caused by the study.

1. € 450.000,-- (i.e. four hundred and fifty thousand Euro) for death or injury for each subject who participates in the Research;
2. € 3.500.000,-- (i.e. three million five hundred thousand Euro) for death or injury for all subjects who participate in the Research;
3. € 5.000.000,-- (i.e. five million Euro) for the total damage incurred by the organisation for all damage disclosed by scientific research for the Sponsor as 'verrichter' in the meaning of said Act in each year of insurance coverage.

The insurance applies to the damage that becomes apparent during the study or within 4 years after the end of the study.

### **9.5 Incentives**

Subjects will receive a financial compensation of 75 euro per 24 hours. They will receive 450 euro in total after completion of the study. For the additional test day subjects receive 100 euro extra, this means a total of 550 euro. Possible travel expenses (maximum € 0.19 per km) will be reimbursed.

## **10. ADMINISTRATIVE ASPECTS AND PUBLICATION**

### **10.1 Handling and storage of data and documents**

Subjects' personal information will be confidentially handled during the study, according to the Dutch Personal Data Protection Act (Wet bescherming persoonsgegevens; Wbp). Results will be linked to the intervention and not to individual subjects. Subject numbers (e.g. number 1) in combination with treatment codes (5En% protein, code A; 30En% protein, code B) will be used throughout the study. Only the researchers are familiar with subject information, so privacy of personal information is guaranteed. If desirable, subjects will be informed about their personal study results at the end of the study. Collected body material (urine and blood) will be destroyed after publication of the results. Personal data will be kept for a period of 15 year, which is the legal time to keep medical data. Hereafter the data will be destroyed.

### **10.2 Amendments**

Amendments are changes made to the research after a favourable opinion by the accredited METC has been given. All amendments will be notified to the METC that gave a favourable opinion.

A 'substantial amendment' is defined as an amendment to the terms of the METC application, or to the protocol or any other supporting documentation, that is likely to affect to a significant degree:

- the safety or physical or mental integrity of the subjects of the trial;
- the scientific value of the trial;
- the conduct or management of the trial; or
- the quality or safety of any intervention used in the trial.

All substantial amendments will be notified to the METC and to the competent authority.

Non-substantial amendments will not be notified to the accredited METC and the competent authority, but will be recorded and filed by the sponsor.

### **10.3 Annual progress report**

The sponsor/investigator will submit a summary of the progress of the trial to the accredited METC once a year. Information will be provided on the date of inclusion of the first subject, numbers of subjects included and numbers of subjects that have completed the trial, serious adverse events/ serious adverse reactions, other problems, and amendments.

**10.4 End of study report**

The investigator will notify the accredited METC and the competent authority of the end of the study within a period of 90 days. The end of the study is defined as the last patient's last visit.

In case the study is ended prematurely, the sponsor will notify the accredited METC and the competent authority within 15 days, including the reasons for the premature termination. Within one year after the end of the study, the investigator/sponsor will submit a final study report with the results of the study, including any publications/abstracts of the study, to the accredited METC and the Competent Authority.

**10.5 Public disclosure and publication policy**

The CCMO Statement publication policy will be followed to publish research results after the end of the study.

